### Data

The data collection strategy is informed by the SDR theory of change (Fig. 1), which has multiple pathways. According to the reform logic, in sub-countries where SDR has been implemented, pregnant women will change their care-seeking behavior by shifting their place of delivery from home or primary care clinics to delivery hub hospitals. The extent of this shift in care-seeking behavior will be measured by the main survey of enrolled pregnant women, hereafter referred to as the *pregnancy registry*. A second component of the theory of change is that delivery hubs, having been upgraded with better equipment, infrastructure, and staff, will deliver high quality intrapartum, postpartum, and newborn care. For the subset of women and newborns with life-threatening conditions (obstructed labor, sepsis, postpartum hemorrhage, low birthweight, birth asphyxia), timely and appropriate treatment will save lives, resulting in less maternal and newborn mortality and morbidity. We will measure both elements of this theory of change. Place of delivery and ultimate health outcomes will be measured through the pregnancy registry. Quality of care provided will be measured through facility and provider surveys, direct observations of deliveries, and women’s reports of quality from a subset of the main survey.

#### Pregnancy registry

The main data collection tool to measure the primary outcomes will be the pregnancy registry survey, which includes both enrollment at ANC and post-delivery follow-up surveys. All eligible, consenting pregnant women presenting for ANC in the 72 participating facilities (except the excluded categories mentioned above) will be enrolled.^2^ At this visit, basic demographic information, anticipated delivery date, preferred and previous delivery locations, self-reported and formally diagnosed antenatal complications, and detailed contact and tracking information will be collected. Participants will be contacted by phone 7 days after their anticipated delivery date and again 28 days after their expected delivery date. In these interviews, details regarding maternal health and child survival and mother’s delivery experience will be collected, as well as mothers’ receipt of post-natal care, satisfaction with delivery care, and OOP costs for delivery including transportation costs. In-person follow up visits will be conducted (using tracking information collected at enrollment) if respondents cannot be reached by phone.

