#### Longitudinal survey

A subset of 2,000 respondents from the pregnancy registry will be invited to take part in a more detailed follow up with multiple interviews over the course of their pregnancy and immediate postpartum period. Interviews for this survey (known as the *longitudinal survey*) will take place in a random subset (40 out of 72) of sampled facilities. Approximately 3% of all enrolled women will be randomly sampled within the pregnancy registry at enrollment for participation in the longitudinal survey. This survey will be conducted, in person, at the antenatal care facility at enrollment; over the phone during the month 8 of pregnancy, 7 days after her anticipated delivery date, and 28 days after delivery; and again in person at the participant’s home 2 months after delivery. These surveys will allow deeper investigation of topics including: previous pregnancies, quality of antenatal, delivery and post-natal care, delivery location intention at various points in pregnancy and reasons for same, travel modality and time to delivery hubs, socioeconomic status, awareness of SDR, and opinions about the health system. Basic anthropometrics and biomarkers (height/weight, blood glucose, hemoglobin and blood pressure) and will also be collected at enrollment and at the final follow up. For newborns, anthropometrics will be captured at the final follow up visit.

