### Outcomes

#### Impact evaluation: primary outcomes

The primary outcome of this study is a composite measure of maternal and neonatal mortality. This composite was selected, following similar trials (e.g. Semrau et al. 2017) because SDR is hypothesized to improve both maternal and neonatal outcomes, and because the individual components of this measure would likely not occur frequently enough to allow us to reliably detect changes within the population of Kakamega County. Compared to the composite used in similar trials [7], we omit the “maternal near miss” element from the composite outcomes, due to the difficulty is accurately assessing near miss based on retrospective self report [14]. We estimate a baseline prevalence of the composite indicator of 4% in Kakamega County.

This composite measure reflects severe maternal, fetal, and neonatal adverse events that occur around the time of childbirth relative to the total number of birth events. For this study, a birth event is defined as the period from the time of maternal admission for childbirth (or the onset of labor, for home deliveries) until the completion of 28 days after birth. A birth event considers the mother and baby to be a single dyad given that their health outcomes are many times interdependent. For this reason, multiple gestations will also be considered to be a single birth event. A birth event may result in a stillbirth and/or a live birth.

Specific outcomes comprising the composite measure are:

A.Maternal death at 28 days: defined as death of a woman at any time from onset of labor, through delivery, until the period of 28 days following delivery.B.Intrapartum stillbirth: defined as death during labor >  = 28 weeks gestation, as evidence by lack of maceration and by a reporting of fetal movements in the two days before labor.C.Neonatal mortality: defined as a newborn death that occurs within the first 28 days of life.

The composite outcome will be assessed through the two follow up phone surveys from the pregnancy registry, and in person surveys when respondents cannot be reached by phone.

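### The last registry contact is timed from the expected delivery date, while the 28-day primary outcome runs from actual delivery, so births after the expected date are under-followed

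*Protocol article*

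**What the plan says.** **Outcome window.** Under Impact evaluation: primary outcomes, a birth event lasts "until the completion of 28 days after birth". Maternal death counts "until the period of 28 days following delivery", and neonatal mortality is "defined as a newborn death that occurs within the first 28 days of life". All three run from the actual birth.

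**Source of the outcome.** The same section states: "The composite outcome will be assessed through the two follow up phone surveys from the pregnancy registry". In-person surveys are added for women who cannot be reached by phone.

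**Timing of the contacts.** The Pregnancy registry section states: "Participants will be contacted by phone 7 days after their anticipated delivery date and again 28 days after their expected delivery date". The date is a prediction, because enrolment collects "basic demographic information, anticipated delivery date, preferred and previous delivery locations". The back-up visit depends on failed contact, not on the baby's age: "In-person follow up visits will be conducted (using tracking information collected at enrollment) if respondents cannot be reached by phone".

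**The other instrument.** The Longitudinal survey section places its postpartum calls "7 days after her anticipated delivery date, and 28 days after delivery" and adds a home visit two months after delivery. That survey covers about 2,000 women, roughly 3% of those enrolled.

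**Missing outcomes.** The Analysis section plans repeated tracking, then multiple imputation of outcomes coded as missing. It does not mention a woman who is reached before her 28 days are complete.

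**The concern.** The endpoint and its measurement start from different days. For a birth on or before the expected date, the last contact falls at or after day 28 and the window is complete. For a birth after the expected date, the window is cut short by exactly the delay. Deaths of mother or baby in the remaining days have no scheduled contact at which they could be reported.

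This concerns the primary outcome, and follow-up that was not observed can be recovered only by contacting the woman again. If the shortfall is alike with and without the reform, the event rate is understated and some power is lost. If it differs, the effect estimate is affected too. A difference is conceivable: the reform moves deliveries into hospitals with surgical capacity, the caesarean rate is tracked as an adoption indicator, and delivery timing relative to the expected date could shift.

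**Working it through.** The plan gives no figure of its own on this point, so there is none to reproduce.

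**Step 1. Date arithmetic (no assumptions).** Let d = actual delivery date − expected delivery date, in days. Age at the last scheduled contact = 28 − d.

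| d (days) | Age at last contact (days) | Window complete? |
|---|---|---|
| −7 | 35 | yes |
| 0 | 28 | yes |
| 7 | 21 | no |
| 14 | 14 | no |
| 21 | 7 | no |
| 28 | 0 | no |
| over 28 | not yet born | no |

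**Step 2. Share of births affected (assumed).** Take d as Normal(mean, SD). The share without a full 28 days is P(d > 0), and the share undelivered at the last contact is P(d > 28).

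**Step 3. Share of neonatal deaths missed among babies already born (assumed).** Let L = 25–35% be the share of neonatal deaths on days 7–28, spread evenly. If first-week deaths fall close to birth, the missed share is L × A, where A is the average of min(d, 21)/21 over births with 0 < d ≤ 28 (all other births contribute zero).

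| Mean, SD | P(d > 0) | P(d > 28) | A | L = 25% | L = 35% |
|---|---|---|---|---|---|
| −3, 10 | 38% | 0.1% | 0.125 | 3.1% | 4.4% |
| −3, 14 | 41% | 1.3% | 0.175 | 4.4% | 6.1% |
| 0, 14 | 50% | 2.3% | 0.224 | 5.6% | 7.8% |
| −3, 21 | 44% | 7.0% | 0.199 | 5.0% | 7.0% |

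The range is about 3–8%. Spreading first-week deaths evenly over the week instead raises the top to about 9%. Of the planned 59,753 mothers, 38–50% is about 22,800 to 29,900 without a complete window.

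**Step 4. Conversion to the composite.** The Setting section gives neonatal mortality of 19 per 1,000 live births and the Power calculations section a composite rate of 40.6 per 1,000 births. The ratio is 19/40.6 = 0.47. The two rates come from different sources, so this share is illustrative. The loss is then 0.47 × 3.1% = 1.5% up to 0.47 × 7.8% = 3.7% of composite events, or about 1.5–4%. Intrapartum stillbirth is not truncated for any woman who has delivered. Maternal deaths are truncated in the same way but are not included in this figure.

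**Step 5. Effect on the comparison.** With equal missed shares, the factor (1 − missed share) cancels from the ratio. For a differential example, let SD = 14, with mean 0 without the reform and −3 under it, and a true ratio of 0.875 (the plan's 12.5% reduction). With L = 35%, the observed ratio is 0.875 × (1 − 0.468 × 0.0614)/(1 − 0.468 × 0.0783) = 0.882. With L = 25% it is 0.880. If first-week deaths are spread evenly and deaths among women undelivered at the contact also count as missed, it is 0.886–0.888. In each case the benefit looks slightly smaller than it is.

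**The case against.** **The sentence may be loose condensation.** It uses two words for one predicted date, the longitudinal text times its comparable call from delivery, and a full protocol not shown here could tell callers to reschedule once the true date is known. That is fair, and a drafting slip cannot be excluded. But the article uses the two anchors separately for the two instruments, and it gives the predicted one to the registry that measures the primary outcome. The sections need reconciling in either case.

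**Actual contacts will often be late.** Several attempts and home visits are planned, so some babies will be past day 28 when the mother is reached. This softens the shortfall but does not remove it, because delay follows from failed contact and not from the baby's age.

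**Stronger readings that the documents do not support:**

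- A reader might set the loss beside the 12.5% target effect. In the widest scenario (mean −3, SD 21) the total reaches 14–16% of neonatal deaths. But the target is a reduction in the whole composite, and that total includes deaths among the 7% of births still to come at the call. Those women would be seen as undelivered.
- A reader might infer that women reached early are recorded as event-free. The article gives no coding rule for them, so this is an inference. The gap is that nothing rules it out.
- A reader might expect a spurious benefit. The mechanism considered here, earlier delivery under the reform, lengthens follow-up in the exposed group and works the other way.

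**Conclusion.** The mismatch holds on the text alone: the outcome window starts at delivery, the last contact is counted from the predicted date, and no rule shown closes the gap. Its size rests entirely on the assumed dating error and timing of deaths. On those assumptions it is moderate: a large minority to half of births lack a full window, but few composite events are lost. The main consequence is an understated event rate. Bias in the treatment effect is conditional on a difference in timing by exposure. In the example worked here it moves the observed ratio by roughly 1–1.5%, towards masking benefit. The point deserves correction because it concerns how the primary endpoint is ascertained and the remedy is simple, not because it threatens to overturn the result.

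**What to change.** 1. Record the actual delivery date at the first postpartum call, and schedule the final registry contact at 28 or more completed days after it.
2. Re-call women who have not delivered at either contact, until the delivery date is known and the window has closed.
3. State that a last contact before day 28 with no event is incomplete follow-up: re-contact the woman, or handle the 28-day outcome as missing or censored. Apply this to interviews already done, since enrolment began in February 2022.
4. Bring the Pregnancy registry, Longitudinal survey and primary outcome sections into line. If callers already reschedule from the delivery date, correcting the sentence and adding the rule in item 3 is enough.

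The cost is a change to the call schedule, some extra calls, and a longer wait for the final contact of women who deliver late.

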#### Longitudinal survey

A subset of 2,000 respondents from the pregnancy registry will be invited to take part in a more detailed follow up with multiple interviews over the course of their pregnancy and immediate postpartum period. Interviews for this survey (known as the *longitudinal survey*) will take place in a random subset (40 out of 72) of sampled facilities. Approximately 3% of all enrolled women will be randomly sampled within the pregnancy registry at enrollment for participation in the longitudinal survey. This survey will be conducted, in person, at the antenatal care facility at enrollment; over the phone during the month 8 of pregnancy, 7 days after her anticipated delivery date, and 28 days after delivery; and again in person at the participant’s home 2 months after delivery. These surveys will allow deeper investigation of topics including: previous pregnancies, quality of antenatal, delivery and post-natal care, delivery location intention at various points in pregnancy and reasons for same, travel modality and time to delivery hubs, socioeconomic status, awareness of SDR, and opinions about the health system. Basic anthropometrics and biomarkers (height/weight, blood glucose, hemoglobin and blood pressure) and will also be collected at enrollment and at the final follow up. For newborns, anthropometrics will be captured at the final follow up visit.

#### Delivery hub facility surveys, provider assessments, and delivery observations

Facility audits and provider assessments will be conducted in planned delivery hubs and all other level 4 and level 5 hospitals (*n* = 14) four times over the study period: once six months before the start of phase 1, once at the start of each of the three waves of SDR implementation. These surveys will measure capacity for deliveries, structural quality, and process quality of care of each delivery hub before and after re-design is implemented. For example, the survey will measure the number of maternity beds, the presence of a newborn unit, the number and functionality of operating theaters, presence of staff (including all medical doctors by specialty, as well as clinical officers, nurse-midwives, nurses, and other cadres), the availability of 24 h care, the presence of both basic and comprehensive emergency obstetric signal functions including procedures, equipment, and medicines. These surveys will also measure provider knowledge and attitudes both before and after the redesign, with particular focus on the management of common obstetric complications, and will also assess working conditions, motivation, and awareness of SDR implementation. All providers who are working in the maternity or newborn care units the day of the facility assessment will be invited to participate in the survey.

Enumerators who are trained in doing deliveries (i.e. nurses or midwives) will conduct continuous observations of deliveries for one week in each delivery hub (*n* = 10) at four times over the study. Observations will be used to assess the technical and interpersonal quality of care from the time women are admitted to the labor ward until approximately 6 h after her delivery or her discharge from the facility. Observations will be conducted 6 months before the start of phase 1, and once at the start of each of the three waves of SDR implementation. Given current volumes in delivery hubs from administrative data, an estimated 1,500 deliveries will be observed over the course of the study.

#### Primary care facility survey and provider assessment

Facility and provider surveys will also be conducted in a random sample of 40 primary care (i.e. non-delivery hub) facilities will take place twice: during the baseline period and at the end of phase 1. The purpose will be to examine the capacity and readiness of antenatal care providers and facilities, their skills, job satisfaction, and the resources, drugs, and equipment that they have to do their work, and how this changes over the initial period of SDR implementation. All providers that provide antenatal, postnatal, or maternity care who are working the day of the facility assessment will be invited to participate.

### Outcomes

#### Impact evaluation: primary outcomes

The primary outcome of this study is a composite measure of maternal and neonatal mortality. This composite was selected, following similar trials (e.g. Semrau et al. 2017) because SDR is hypothesized to improve both maternal and neonatal outcomes, and because the individual components of this measure would likely not occur frequently enough to allow us to reliably detect changes within the population of Kakamega County. Compared to the composite used in similar trials [7], we omit the “maternal near miss” element from the composite outcomes, due to the difficulty is accurately assessing near miss based on retrospective self report [14]. We estimate a baseline prevalence of the composite indicator of 4% in Kakamega County.

This composite measure reflects severe maternal, fetal, and neonatal adverse events that occur around the time of childbirth relative to the total number of birth events. For this study, a birth event is defined as the period from the time of maternal admission for childbirth (or the onset of labor, for home deliveries) until the completion of 28 days after birth. A birth event considers the mother and baby to be a single dyad given that their health outcomes are many times interdependent. For this reason, multiple gestations will also be considered to be a single birth event. A birth event may result in a stillbirth and/or a live birth.

Specific outcomes comprising the composite measure are:

A.Maternal death at 28 days: defined as death of a woman at any time from onset of labor, through delivery, until the period of 28 days following delivery.B.Intrapartum stillbirth: defined as death during labor >  = 28 weeks gestation, as evidence by lack of maceration and by a reporting of fetal movements in the two days before labor.C.Neonatal mortality: defined as a newborn death that occurs within the first 28 days of life.

The composite outcome will be assessed through the two follow up phone surveys from the pregnancy registry, and in person surveys when respondents cannot be reached by phone.

#### Impact evaluation: secondary outcomes

Secondary outcomes of the study include patients’ satisfaction with care received and confidence in the health system, the location of care (health center versus hospital), OOP expenditures, quality of delivery care, travel time, self-reported maternal complications, and equity on all of these dimensions between women.

Women’s satisfaction with the care that they receive will be measured in the pregnancy registry, and with more detail, in the longitudinal survey. Total OOP expenditures will be measured using seven questions capturing expenditures on transportation, overnight lodging, medical fees, registration, drugs and supplies, medical tests, food, and any other costs. These will be summed to create an OOP expenditures indicator. Quality of care will be measured using both women’s perceived quality as well as through observations of care in delivery hubs. Perceived quality ratings will include women’s ratings on technical quality and respectful care quality for delivery as well as for ANC and postnatal care (PNC). Using the observations of delivery care, technical quality of routine care will be assessed through a 20-item index capturing the processes of intrapartum and immediate postpartum care [15]. Respectful care will be measured using a 10 item index measuring provider actions, such as whether or not a provider explains procedures before proceeding [16]. Care utilization will be measured with both the facility utilization rate, the delivery hub utilization rate, as well as ANC and PNC utilization, using the pregnancy registry. Additional data from the Kenyan Health Information System (KHIS) will be used to compare delivery hub utilization rates between enrolled and non-enrolled pregnant women during the study period. Maternal complications will be defined through the self report of one of the following: fits (in absence of history of epilepsy), loss of consciousness for > 1 h, high fever with chills and foul-smelling discharge, blood transfusion, hysterectomy, intensive care unit admission, mechanical ventilation, or hospital stay of > 7 days. Gaps in access and outcomes by education, proximity to delivery hubs, and household socio-economic status will be compared for the satisfaction, utilization, and cost outcomes described above in implementation sub-counties versus control sub-counties.

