### The intervention

SDR for maternal and newborn health is a multi-component health system reform. In Kakamega, SDR is being implemented by the County Department of Health, with support from the non-governmental organization (NGO) Jacaranda Health. Financing is from the County government and is supplemented by the Bill and Melinda Gates Foundation.

An initial feasibility assessment study examined the existing capacity, facility accessibility, political will and potential benefits of SDR in Kakamega County [13]. Based on this assessment, the County identified several components for a health system reform. First, it selected ten hospitals to serve as delivery hubs across the county. These were all public facilities; typically sub-county hospitals (level 4 hospitals in the Kenyan system). Before the intervention, the delivery hubs all conducted 1,000 or more deliveries per year, but not all had comprehensive emergency capabilities.

The first component of SDR is a preparation phase, in which delivery hubs are strengthened (Fig. 1) and prepared for the higher patient volumes that will result from the SDR policy change of encouraging delivery at delivery hubs. This includes deployment of additional staffing, as well as improvements to infrastructure and equipment. For example, designated delivery hub hospitals in Kakamega are scheduled to be staffed with additional nurses, doctors, and specialists: In addition to their pre-existing complement of medical officers, the current plan is for each delivery hub in Kakamega to have a surgeon, a pediatrician, an obstetrician-gynecologist, and a specialist medical officer posted to the facility to bolster delivery care.

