**Fig. 1 Fig1:**
[figure not shown]
Service Delivery Redesign Theory of Change

On the infrastructure side, each delivery hub will have operating theaters built or improved, maternity wards expanded, and newborn units built or expanded. Facility capacity to deliver blood transfusions will also be augmented.

Delivery hubs are further from most women's homes than local clinics; traveling greater distances to deliver can be difficult, especially at night. In Kakamega's SDR reform, this issue will be addressed with the participation of the NGO Rescue.co, who contracts with private transport providers to provide emergency transport for pregnant women.

When delivery hubs are upgraded to a level that will enable higher patient volumes and improved quality of care, and complementary interventions such as emergency transport and facility financing reforms are in place, the government of Kakamega plans to communicate to all health workers, and all health system users, that policy regarding place of delivery has changed, and women are now expected to deliver at designated delivery hub hospitals. To this end, the last component of the intervention is this public communication element, which will be undertaken through media campaigns and public outreach meetings, as well as direct communication from health workers to antenatal care (ANC) clients.

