### Research questions

#### Impact evaluation component

The main research question of the impact evaluation (effectiveness) component of this study is the impact of SDR in Kakamega County on maternal and newborn health, measured using a composite indicator of maternal and newborn health. The secondary research question examines the impact of SDR on patient satisfaction and perceived quality of care, maternal complications, out-of-pocket (OOP) expenditures, and utilization of care.

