#### Implementation evaluation: direct and indirect outcomes

For the implementation science component of the study we will measure coverage, adoption, and fidelity of SDR implementation using survey, administrative, and program data on activities and outputs. We will track indicators on program reach (e.g. percentage of primary care clinics where women are routinely advised to deliver at delivery hubs; percentage of women who report being advise to deliver in delivery hubs); adoption (e.g. percentage of women delivering at delivery hubs; percentage of delivering at health centers; labor and delivery quality of care; ANC and PNC utilization and quality; C-section rate); and intervention fidelity (maternity ward and newborn unit expansions in delivery hub hospitals; specialist physician and nurse staffing levels; maternity and newborn staff knowledge levels; availability of critical inputs such as blood for transfusions).

Given the size and scope of the policy reform, it is likely that SDR will affect the health system in indirect ways, beyond the hypothesized effects on maternal and newborn health services. Complex system-level reforms can have both positive and negative broader systemic effects. Therefore we will measure potential system-level effects of SDR as secondary implementation outcomes (Table 1).

**Table 1 Tab1:** Implementation evaluation indicators

Direct effects: Implementation evaluation		
Reach	% ANC clinics where women are routinely advised to deliver at delivery hubs	Primary care facility survey
	Percentage of women who report being advised to deliver in delivery hubs	Longitudinal survey
Adoption	% women delivering at delivery hubs	Pregnancy registry; KHIS
	% women delivering at primary care facilities	Pregnancy registry; KHIS
	Delivery quality of care	Delivery observation checklist
	ANC and PNC utilization	Pregnancy registry; KHIS
	Caesarean section rate	Pregnancy registry; KHIS
Fidelity	Maternity ward and newborn unit capacity in delivery hub hospitals	Delivery hub survey
	Maternity and newborn staff knowledge levels	Delivery hub and primary care provider assessments
	Availability of critical inputs (e.g. blood for transfusions)	Delivery hub facility survey
	Specialist physician and nurse staffing levels	Delivery hub facility survey
Indirect effects: Implementation evaluation		
Indirect effects	Utilization for non-MNCH services (e.g. HIV, TB) from hospital congestion	KHIS

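### The secondary outcome of maternal complications mixes morbidity with access to care: five of its eight items record care received, so at constant need SDR biases it upward

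*Protocol article*

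**What the plan says.** All references are to the protocol article; the SAP is not shown.

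- Under Impact evaluation: secondary outcomes, one positive answer is enough: "Maternal complications will be defined through the self report of one of the following". Three items are symptoms or signs: fits without a history of epilepsy, loss of consciousness for more than 1 hour, and "high fever with chills and foul-smelling discharge". The other five are "blood transfusion, hysterectomy, intensive care unit admission, mechanical ventilation, or hospital stay of" more than 7 days. No item is conditioned on need or on place of delivery.
- Under Research questions, the impact of SDR on this outcome is part of the secondary question, which lists "maternal complications, out-of-pocket (OOP) expenditures, and utilization of care".
- The intervention section states: "Facility capacity to deliver blood transfusions will also be augmented". It also says that "each delivery hub will have operating theaters built or improved, maternity wards expanded, and newborn units built or expanded", and plans for "each delivery hub in Kakamega to have a surgeon, a pediatrician, an obstetrician-gynecologist, and a specialist medical officer".
- The Data section expects births to move from home and primary care clinics to hub hospitals. The Discussion gives the aim as moving all facility deliveries to the ten hubs.
- Among the implementation outcomes, fidelity includes "availability of critical inputs such as blood for transfusions".
- Under Secondary analyses, maternal complications are analysed in the same way as the primary outcome.

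**The concern.** The intervention changes the chance that a woman in need receives the care that makes her a case. Take two women with the same haemorrhage. One delivers where there is no blood, is not transfused and has none of the other items; she is a non-case. The other is transfused in an upgraded hub; she is a case. The morbidity is the same and the recorded outcome differs because of exposure.

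The protocol also scores closely related facts in opposite directions. Blood being available counts as successful implementation, while a woman receiving blood counts as a complication.

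Nothing in the stated analysis separates need from access. The adjustment covariates are education, age, parity, transport time, season and perceived risk. The planned validation against facility records tests whether self-report is accurate, and an accurately reported transfusion still carries the problem. What is at stake is the reading of one secondary outcome: a benefit could be missed, or met need could be taken for harm.

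**Working it through.** The protocol states no rate, effect size or power for this outcome, so there is no figure to reproduce. The check has two parts.

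**1. Items against the documented content of SDR**

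| Item | Type | Link to SDR in the protocol |
|---|---|---|
| Fits | symptom | not a service |
| Loss of consciousness | symptom | not a service |
| Fever with discharge | symptom | not a service |
| Transfusion | care | named explicitly |
| Hysterectomy | care | inferred from theatres, surgeon, obstetrician-gynecologist |
| Stay over 7 days | care | inferred from ward expansion and the shift to hospital |
| ICU admission | care | not named; at most covered by the Background's general mention of other advanced services |
| Mechanical ventilation | care | as for ICU admission |

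Five of the eight items are care received. One is tied to SDR explicitly, two by fair inference, and two are undocumented.

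**2. Illustration of direction and possible size**

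Recorded rate = (1 − d) × [s + t × f], with f = h + (1 − h) × r.

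- h: share delivering in hospital. Baseline 0.37 (Setting section, all county births in 2018). After SDR, assumed 0.50, 0.65 or 0.80.
- r: chance that a woman in need who delivers elsewhere still reaches the treatment. Assumed 0.25, 0.50 or 0.75.
- s, t: rate of the symptom items and of need for the care items, taken as non-overlapping. Both assumed.
- d: true proportional reduction, applied to both parts. Assumed 0, 0.125 or 0.25.

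Women in need who deliver in hospital are taken as treated both before and after SDR, so only the change of place acts; the upgrade of the hubs themselves is left out.

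Change in the care items alone, d = 0:

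| r | f at baseline | h = 0.50 | h = 0.65 | h = 0.80 |
|---|---|---|---|---|
| 0.25 | 0.5275 | +18% | +40% | +61% |
| 0.50 | 0.685 | +10% | +20% | +31% |
| 0.75 | 0.8425 | +4% | +8% | +13% |

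Worked case, s = t = 2%, r = 0.25, h rising to 0.80:

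- Before: 0.02 + 0.02 × 0.5275 = 0.03055.
- After, d = 0: 0.02 + 0.02 × 0.85 = 0.0370, a change of +21.1%.
- After, d = 0.125: 0.875 × 0.0370 = 0.0324, a change of +6.0%.

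Opposite corner, r = 0.75, h rising to 0.50:

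- Before: 0.02 + 0.02 × 0.8425 = 0.03685.
- After, d = 0: 0.02 + 0.02 × 0.875 = 0.0375, a change of +1.8%.
- After, d = 0.125: 0.875 × 0.0375 = 0.0328, a change of −11.0%.

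Range of the recorded change over the whole grid of r and h:

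| s, t | d = 0 | d = 12.5% | d = 25% |
|---|---|---|---|
| 2%, 2% | +1.8% to +21.1% | −11.0% to +6.0% | −23.7% to −9.2% |
| 1%, 3% | +2.8% to +37.5% | −10.1% to +20.3% | −22.9% to +3.1% |
| 3%, 1% | +0.8% to +9.1% | −11.8% to −4.5% | −24.4% to −18.1% |

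In every cell the recorded result lies above the true change. A recorded rise appears only when the constant-need increase exceeds 1/(1 − d) − 1, which is 14.3% for d = 0.125 and 33.3% for d = 0.25.

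**The case against.** A reader might infer that SDR is designed to supply all five care items. The protocol does not support that: adult intensive care and ventilation are never listed as components.

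A reader might also infer that SDR will produce more recorded complications. That does not follow either. The Data section expects timely treatment to reduce morbidity, and earlier care may prevent some hysterectomies, ICU admissions and long stays. Access and prevention pull in opposite directions, and many cells of the illustration show a net fall.

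The haemorrhage example is not absolute. A woman who delivers at home and is later transfused, or stays over 7 days, is still a case.

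There is some mitigation. The outcome is secondary; the primary composite of deaths and intrapartum stillbirth contains none of these items. The research question does not say that lower is better. Delivery location, caesarean rate and blood availability are tracked and would help in interpreting a rise. Item-level reporting may also be set out in an SAP.

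Finally, making the three symptoms the outcome would lose something. None of them directly captures haemorrhage or obstructed labour, both of which the Data section names as conditions that SDR is meant to treat.

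These points limit the claim and shape the remedy. They do not remove the core: the definition is fixed in the protocol, it mixes need with access, and the stated analysis does not separate them.

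**Conclusion.** The concern holds in a limited form. Five of the eight items record care received; the link to SDR is explicit for transfusion and plausible for hysterectomy and long stay. At constant need, the outcome is biased upward whenever hospital delivery makes such care more likely. It can therefore understate or hide a real fall in morbidity and, when care items dominate or the shift to hospital is large, reverse it.

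The size is unknown. The percentages above rest on assumed rates, an assumed chance of reaching care from outside hospital, assumed hospital shares after SDR, and no overlap between items; only the 37% baseline share is documented. They show direction and plausibility, and are not estimates. Neither a certain net rise nor an outcome that is useless for the secondary question can be concluded from the protocol.

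**What to change.** Keep the eight-item composite and add to the plan, before outcome results are seen:

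1. The three symptom items and the five care items are each analysed and reported separately, with the same model as the composite.
2. The care items are interpreted as utilisation, with no presumption that a lower rate is better.
3. A rise in the composite is not read as harm unless the symptom items also rise.

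This uses the same survey questions and costs only wording and two further analyses. The plan should state the downside. The symptom-only result has fewer events, is less comparable with near-miss definitions, and does not directly capture haemorrhage or obstructed labour. It should therefore stand beside the composite and not replace it, and a flat symptom result does not by itself rule out a change in those conditions.
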